## 11.4 Interim analyses

The trial will be reviewed by the PENTA Independent Data Monitoring Committee (IDMC). No member of the PENTA or BREATHER Steering Committees or any clinician (investigator) responsible for the clinical care of trial participants may be a member of the IDMC. The IDMC will review the trial in all aspects, including the number of participants to be recruited. The IDMC reviewed the data from the pilot phase and identified no safety concerns and recommended recruitment continue. It will continue to review data at regular intervals (approximately every 6 months), in strict confidence, considering the findings from other relevant studies, and will advise the TSC. During the main phase of the trial they will review the trial in all aspects including data from both arms. The IDMC should inform the Chair of the TSC if, in their view, the results provide either:

(a) unequivocal evidence\* which is likely to convince a broad range of HIV clinicians, including the study investigators, that, one of the two treatment strategies (Continuous Therapy or Short-Cycle Therapy) is performing poorly for all participants or for a particular category of participants, and there is a reasonable expectation that this new evidence will materially influence patient management;

or

(b) good evidence\* that Continuous Therapy is superior to Short-Cycle Therapy in terms of the primary outcome and the non-inferiority of Short Cycle Therapy is extremely unlikely to be demonstrated with continued enrolment and/or follow-up.

\* The criteria for the strength of evidence cannot be defined precisely and is left to the judgement of the IDMC. However, as an example, if in an interim analysis the 99% confidence interval for the hazard ratio for the primary outcome excluded 1, this may be considered as providing good evidence of a difference in risk between the two groups. If, the 99.9% confidence interval also excluded 1, this may be regarded as providing unequivocal evidence of a difference between the two groups.

## **11.5 Pilot phase**

Once the 15th participant randomised to the SCT arm has been recruited to the pilot phase, recruitment and randomisation will be put on hold in both arms.

If full data (weekly viral loads for first 3 weeks) are not obtained on all young people in the SCT arm of the pilot phase, further participants will be enrolled in the pilot phase. This will be assessed in real-time rather than waiting until the end of the pilot phase.

The IDMC will review the results of the pilot phase and consider the findings in conjunction with other relevant studies. Formal stopping criteria for the pilot phase, e.g. the Haybittle-Peto rule, will not be used as the pilot phase is not assessing the efficacy of the SCT strategy compared to the continuous therapy. The aim of the pilot phase is to make sure the SCT strategy does not result in a high proportion of young people with increased viral loads ( $\geq 50$  c/ml) off ART in the first few weeks. Therefore the following situation seen in the SCT arm would cause concern regarding continued enrolment:

- 5 (or more) participants who have an HIV-1 RNA  $\geq 50$  c/ml (validated by a HIV-1 RNA  $\geq 50$  c/ml on the same sample) at weeks 1, 2 or 3 would following weekend interruption and before restarting ART give evidence that viral load suppression rates on an SCT strategy in general would be  $<90\%$  (10/15 suppressed = 66%, 95% exact CI=38%, 88%). This would be considered an unacceptable rate of viral load suppression.

If 4 (or less participants) have an HIV-1 RNA  $\geq 50$  c/ml (validated by a HIV-1 RNA  $\geq 50$  c/ml on the same sample) at weeks 1, 2 or 3 would give some evidence that viral load suppression rates on an SCT strategy would be  $>90\%$  (11/15 suppressed = 73%. 95% exact CI=45%, 92%) and therefore would provide reassurance to continue enrolment.

There will not be any further recruitment until this review has taken place. Following the review of the pilot phase, the IDMC will make recommendations to the TSC, who will decide whether to continue the trial. If the decision is to continue the trial, recruitment will re-commence.

## **11.6 Analysis plan**

Intention-to-treat analyses will be performed on all randomised participants. Statistical methods include:

- Descriptive statistics for the summary of baseline characteristics
- Fishers exact test and logistic regression models for the analysis of binary outcome variables
- Analysis of variance and linear regression models for the analysis of continuous outcome variables, adjusting for baseline
- Poisson regression for the analysis of the incidence rate of clinical/adverse events
- Log rank test and proportional hazards regression models for the analysis of time to event variables

The incidence rate of clinical/adverse events will be summarised by body system and randomised arm. First events (in terms of time to first event) and all events will be considered.

Major resistance mutations will be defined by the current IAS-USA list.

The primary outcome for the main study is HIV-1 RNA  $\geq 50$  c/ml (confirmed on a separate sample within 1 week) at any of week 4, 12, 24, 36 or 48. This outcome only considers HIV-1 RNA measurements at these time points due to the difference in viral load monitoring in the pilot phase and the main trial. However if a young person enrolled in the pilot phase has an HIV-1 RNA  $\geq 50$  copies/ml at weeks 1, 2 or 3 (reproducible on the same sample) or at week 8 (confirmed on a separate sample within 1 week) they will be considered as reaching the primary outcome at week 4 and 12 respectively. All participants will be analysed in the arm to which they were randomised (intention to treat).

A full Statistical Analysis Plan (SAP) will be developed as a separate document.

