## **1.6 Duration**

Young people will be recruited over 27 months and followed until the last randomised participant has completed 48 weeks of follow-up, at which point the main trial will be considered complete. Participants being followed after week 48 should be seen every 12 weeks until the main trial is complete. Participants randomised to the SCT arm should continue to follow the SCT strategy until the main trial is complete unless the clinician or the family have concerns which the clinician should discuss with the appropriate Trials Unit.

Stable and virologically suppressed young people who were randomised to SCT can continue SCT after completion of the main trial if agreed by the clinician and family at least until the results of the main trial become available. Management of HIV-1 RNA viral load should continue as specified in appendix 15.

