# 11 STATISTICAL CONSIDERATIONS

## 11.1 Method of Randomisation

Randomisation (1:1) will be performed centrally by the MRC Clinical Trials Unit, according to a computer-generated randomisation list, using random permuted blocks, stratified by age at randomisation (8-12, 13-17, 18-24 years) and by African vs. non-African country.

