### **Secondary Outcomes:**

- HIV-1 RNA  $< 50$  c/ml at 24 and 48 week.
- Number of HIV mutations present at week 4, 12, 24, 36 or 48 conferring resistance to drugs taken at randomisation or during the trial
- Change in CD4 (absolute and percentage) from randomisation to 24 and 48 weeks
- Change in ART (defined as any change from the ART regimen at randomisation)
- Grade 3 or 4 clinical and laboratory adverse events.
- ART treatment modifying adverse events (all grades).
- New CDC stage B or C diagnosis or death
- Changes in fasting glucose, cholesterol, triglycerides, LDL, HDL and VLDL levels through 48 weeks
- Adherence, acceptability, and quality of life over 48 weeks as assessed by patient completed questionnaires
- HIV-1 RNA  $\geq 50$  c/ml (confirmed on a separate sample within 1 week) at any time throughout follow up.
- HIV-1 RNA  $< 50$  c/ml at 96 and 144 weeks.
- Adherence over the duration of the trial, as assessed by patient completed questionnaires.
- Change in CD4 (absolute and percentage) from randomisation to 96 and 144 weeks.

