## 11.3 Sample size

This phase II/III trial will enrol a minimum of 160 young people, at least 80 per arm.

Assuming 90% of young people in the continuous ART arm and in the SCT arm maintain HIV-1 RNA  $< 50$  c/ml to week 48, 155 young people will provide at least 80% power to exclude a difference of 12% between the two arms (i.e. to exclude suppression rates of less than 78% in the SCT arm) (one-sided  $\alpha = 0.05$ ) [37]. A minimum of **160 (80 per arm) young people will be enrolled** to allow for loss to follow-up (in previous PENTA trials loss to follow-up has been less than 3%).

The power calculations are based on the assumption that 90% of patients in the continuous ART arm will remain virally suppressed to week 48. Any decrease in this percentage is likely to under

power the study and could lead to an equivocal result, as could other changes to the assumptions. The table below gives an indication of the power to exclude a difference of 12% between the two arms for different sample sizes and levels of suppression in the continuous ART arm:

| Total sample size | Power by level of suppression in control arm |                |                |                |                |                |
|-------------------|----------------------------------------------|----------------|----------------|----------------|----------------|----------------|
|                   | 90% suppressed                               | 89% suppressed | 88% suppressed | 87% suppressed | 86% suppressed | 85% suppressed |
| 160               | 80                                           | 77             | 74             | 72             | 69             | 67             |
| 170               | 82                                           | 79             | 76             | 74             | 72             | 69             |
| 180               | 84                                           | 81             | 79             | 76             | 74             | 72             |
| 190               | 86                                           | 83             | 81             | 78             | 75             | 74             |
| 200               | 87                                           | 85             | 82             | 80             | 78             | 76             |
| 210               | 89                                           | 86             | 84             | 82             | 79             | 77             |

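### Section 11.6 plans Poisson regression and an all-events adverse-event analysis without saying how repeat events in one participant, or same-arm siblings, are handled

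*Combined protocol and SAP*

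**What the plan says.** The list of methods in protocol section 11.6 includes "Poisson regression for the analysis of the incidence rate of clinical/adverse events". For survival-type outcomes it gives "Log rank test and proportional hazards regression models for the analysis of time to event variables". A sentence below the list, following one on summarising event rates by body system and arm, adds: "First events (in terms of time to first event) and all events will be considered". First events are thus defined as a time-to-event variable and fall to log-rank and Cox. That leaves Poisson regression as the only listed method for the rate of all events, repeats included.

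Section 11.6 names no variance estimator: no robust or clustered standard error, random effect, negative binomial model or dispersion check. It closes with "A full Statistical Analysis Plan (SAP) will be developed as a separate document"; that separate document is not part of the text reviewed here.

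The outcomes concerned are secondary (section 11.2). They include "Grade 3 or 4 clinical and laboratory adverse events" and adverse events of any grade that modify treatment. Under section 5.3, eligible siblings enter the same arm; section 11.6 does not mention this.

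**The concern.** Plain Poisson regression takes the variance of each participant's count to equal its mean, and treats one participant's events as independent given the model. Adverse events rarely behave that way, and this trial leaves room for repeats. Events are recorded at every protocol visit, and participants are "followed until the last randomised participant has completed 48 weeks of follow-up" (section 1.6), so early recruits are observed well beyond 48 weeks. Laboratory grade 3 or 4 events come from scheduled repeat bloods, so one persistent abnormality could be counted more than once unless a counting rule prevents it. Participants range from 8 to 24 years of age, come from several countries and take different NRTIs, so equal underlying rates would be surprising. Same-arm siblings are a second possible source of correlation.

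At stake is the reading of the safety comparison. Section 2.6 gives less long-term toxicity as a potential benefit of SCT. Intervals that are too narrow could turn a chance imbalance into an apparent benefit or an apparent harm.

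**Working it through.** **Inputs from the plan.** Allocation is 1:1: "Randomisation (1:1) will be performed centrally by the MRC Clinical Trials Unit" (section 11.1). Arm size: "This phase II/III trial will enrol a minimum of 160 young people, at least 80 per arm" (section 11.3), with a maximum total of 220, so 80 to 110 per arm. The plan states no adverse-event rate, dispersion, power or significance level.

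**The plan's own figure.** The only design calculation concerns the primary outcome. With 90% suppression in both arms, a 12-point margin, one-sided 5% and 80% power, n per arm = 2 × 0.9 × 0.1 × (1.645 + 0.842)² / 0.12² = 77.3. That is about 155 in total, as stated (156 if each arm is rounded up). It reproduces, but says nothing about adverse events; only the arm size is used below.

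**Assumptions.** Mean events per participant, mu, and between-participant variance of the rate relative to its squared mean, theta, are both assumed. So are equal follow-up and a nominal two-sided 5% test.

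**Formulas.** For gamma-Poisson counts, the variance/mean ratio is V = 1 + mu × theta. The model-based Poisson standard error is too small by a factor √V. The true error of the nominal 5% test is 2 × [1 − Φ(1.96/√V)].

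For example, at mu = 1 and theta = 1, V = 2, √V = 1.41, 1.96/1.41 = 1.39, and the error is 16.6%.

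**Results.** Simulation is under the null, 80 per arm, 20,000 replicates.

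| mu | theta | V | √V | Formula | Simulated, plain Poisson | Simulated, participant-level robust |
|---|---|---|---|---|---|---|
| 1 | 0 | 1.0 | 1.00 | 5.0% | 4.7% | 4.8% |
| 0.1 | 0.5 | 1.05 | 1.02 | 5.6% | not run | not run |
| 0.1 | 2 | 1.2 | 1.10 | 7.4% | not run | not run |
| 0.3 | 0.5 | 1.15 | 1.07 | 6.8% | 6.0% | 4.9% |
| 0.3 | 2 | 1.6 | 1.26 | 12.1% | 11.2% | 5.5% |
| 1 | 0.5 | 1.5 | 1.22 | 11.0% | 10.9% | 5.2% |
| 1 | 1 | 2.0 | 1.41 | 16.6% | 16.2% | 5.4% |
| 1 | 2 | 3.0 | 1.73 | 25.8% | 25.7% | 5.6% |

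At 110 per arm with mu = 1 and theta = 1, plain Poisson gives 16.6%, so a larger sample does not help. Across all simulated scenarios, including mu = 2, robust variance gives 4.8% to 5.9%. Comparing the proportions of participants with at least one event gives 4.7% to 5.4%.

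Sibling correlation was not simulated: the documents give no number of sibling sets.

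**The case against.** A reader might infer that the plan commits to standard errors that are wrong. The text does not go that far. It names a regression model and no variance estimator, and Poisson regression with participant-level robust standard errors fits the same wording. The list is introduced as what the methods include, and detail is deferred to a separate SAP, where such an option would normally be written. The all-events sentence also follows one about summaries, so applying Poisson to repeat events is the natural reading rather than an explicit statement. These points stand: the gap is an unstated variance method, not a demonstrated error.

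A reader might also take 11% to 26% as the expected error. The documents do not support that. Participants must have had 12 months of viral suppression and a CD4 count of at least 350, and acute illness and grade 3 or worse creatinine, AST or ALT at screening exclude. Low rates of grade 3 or 4 events are therefore plausible. Reaching V = 3 would need theta = (3 − 1)/0.3 = 6.7 at 0.3 events per participant, or 20 at 0.1. The range has to start at 5%.

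Finally, the planned time-to-first-event analysis is immune to repeats and offers a check on an all-events result driven by a few participants. The illustrative IDMC criteria in section 11.4 concern the primary outcome, not a 5% test on adverse events.

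What the objection does not remove is that, on the text available, Poisson is the only method listed for all events and nothing is said about dependence. Left open until data are seen, the choice of variance could decide which safety differences appear significant.

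**Conclusion.** The point holds as a conditional one. Followed literally with model-based standard errors, the all-events analysis gives intervals that are too narrow by √V whenever participants differ in event rate. Over assumed variance/mean ratios of 1 to 3, the true error of a nominal 5% test runs from 5% to about 26%; for rare events it is only about 6-7%. Where this trial falls in that range cannot be settled from the documents.

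Neither the primary non-inferiority result nor the time-to-first-event analysis is affected by repeat events. The matter is worth correcting because the safety comparison bears on the case for SCT and the remedy is simple, but it does not threaten the trial's main conclusion.

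**What to change.** State in the SAP, before the data are examined, that all-events rate ratios will come from Poisson regression with robust standard errors clustered by participant, or from negative binomial regression, in either case with log person-time as offset. Clustering by family instead of by participant covers siblings as well, since each participant belongs to one family. Negative binomial regression alone deals with differences between participants but not with siblings. Say also when a persisting laboratory abnormality counts as a new event. Keep log-rank and Cox for first events.

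The cost is a sentence or two in the SAP and an option in Stata, which section 4.3 already names for the analysis. Intervals widen where events cluster, by factors of 1.22, 1.41 and 1.73 at variance/mean ratios of 1.5, 2 and 3, and hardly at all where they do not.

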## **2.3 Short-Cycle therapy in adults and adolescents**

Two phase II trials of SCT in adults have recently been reported. Firstly a small single-arm pilot study of 5 days on, 2 days off ART in adults in the USA showed that long-term suppression of viral load could be achieved [28]. Two of 9 patients on PI-based HAART had confirmed virological rebound by 48 weeks compared with 1/10 patients on NVP-containing HAART and 0/8 patients receiving EFV-based regimens. As a result of this pilot, the randomised FOTO (Five On Two Off) trial in 60 adults with viral load <50 c/ml on TDF/ FTC/EFV was conducted comparing daily ART to a strategy of 5 days on, 2 days off treatment. 24-week results were recently reported, showing that all 25 patients in the FOTO arm and 24 of 28 patients (86%) in the daily arm who reached week 24 had viral load <50 c/ml at this time point [29]. Reasons for not reaching 24 weeks were psychological reasons (n=2), time burden (FOTO arm) (3), pregnancy (1), and loss to follow-up (daily ART arm)(1); of note, all had viral load <50 c/ml at discontinuation. There were 6 blips (viral load 50-500 c/ml) in the FOTO arm and 9 in the daily ART arm to week 24; there were no instances of virological failure (confirmed viral load >400 c/ml).

Secondly, in a Ugandan trial [30], 171 adults who had suppressed viral load <50 c/ml on a 3-drug ART regimen were randomised to receive either a week on, week off ART regimen (n=32; this arm of the study was discontinued early), a five-days on, two-days off schedule (SCT) (n=57) or continuous therapy (n=56). The majority of subjects (94%) received an EFV-based regimen. The trial showed that SCT was not inferior to continuous HAART; there were ten cases of failure in the continuous-therapy group (plus one death) and six in the SCT group (failure defined as VL >1000 c/ml, a decrease in CD4 count from randomisation of >30% or CD4 count <100 cells/mm^3, on 2 consecutive occasions through the 72 weeks of follow-up; or at 72 weeks, VL >400 c/ml or

development of an opportunistic infection). Levels of resistance were no different in the SCT group compared to continuous group. For patients on HAART containing stavudine, there was a significant decrease in the incidence of lactic acidosis in the SCT arm compared to continuous therapy.

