### Main Trial:

#### Primary Outcome:

In order to compare the proportion of young people with plasma RNA values  $\geq 50$  copies/ml on SCT compared to continuous ART over 48 weeks, the primary outcome of the trial is:

- HIV-1 RNA  $\geq 50$  copies/ml (confirmed on a separate sample within 1 week) at any of week 4, 12, 24, 36 or 48.

This outcome measure only considers HIV-1 RNA measurements at these time points due to the difference in viral load monitoring in the pilot phase and the main trial. However if a young person enrolled in the pilot phase has HIV-1 RNA  $\geq 50$  copies/ml at weeks 1, 2 or 3 (reproducible on the same sample) or at week 8 (confirmed on a separate sample within 1 week), they will be considered as reaching the primary outcome at week 4 and 12 respectively (see section 11.6).

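### A viral load of at least 50 c/ml without a repeat inside one week is a non-event in the primary outcome, and the plan does not say how early leavers are classified

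*Combined protocol and SAP*

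**What the plan says.** **Event.** In 11.6, and equally in 1.4, 4.2 and 11.2, the primary outcome is an HIV-1 RNA value of at least 50 c/ml "confirmed on a separate sample within 1 week) at any of week 4, 12, 24, 36 or 48". The glossary builds the one-week limit into the word confirmed. The one exception is pilot weeks 1 to 3, where a value reproduced on the same sample counts as an event at week 4.

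**Population and method.** "Intention-to-treat analyses will be performed on all randomised participants". Section 11.6 lists "Fishers exact test and logistic regression models for the analysis of binary outcome variables" and also "Log rank test and proportional hazards regression models for the analysis of time to event variables", and assigns neither to the primary outcome. Section 4.2 introduces that outcome with "In order to compare the proportion of young people with plasma RNA values", which suggests a binary summary. Section 11.4 gives as an example of evidence "if in an interim analysis the 99% confidence interval for the hazard ratio for the primary outcome excluded 1", which suggests time to event.

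**Size.** Section 11.3 needs 155 participants to exclude a 12-point difference (90% suppression in both arms, one-sided alpha 0.05, at least 80% power). It enrols at least 160 to cover loss, put at under 3% in earlier trials of the network.

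**Timing of the repeat.** Sections 1.5, 7.4 and 7.6 require a separate sample within one week in both arms. Section 7.7 holds the repeat back until two weeks after an immunisation. Appendix 15 starts the week when the result is reported, not when the sample is drawn.

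No section classifies a participant who leaves without an event, or a raised value with no valid repeat. Section 11.6 leaves the full SAP to a separate document, which is not part of the text reviewed.

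**The concern.** The trial is sized on the proportion who stay suppressed to week 48, but the outcome registers only a positive finding that has been confirmed in time. Anything unconfirmed falls by default on the suppressed side. Take a participant with 400 c/ml at week 36 and no repeat. A binary analysis counts this person as a success. A time-to-event analysis carries the same person forward event-free. A rebound confirmed ten days after sampling because of 7.7 or Appendix 15 fails the literal definition in the same way, although the site followed the protocol.

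A participant who leaves at week 14 with values below 50 c/ml is a separate case. Under Fisher's test or logistic regression on all randomised, this person counts as suppressed to week 48. Under a log-rank or Kaplan-Meier analysis the person is censored.

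In a non-inferiority trial, removing the same fraction of failures from both arms shrinks a true difference. The risk is that a strategy at or beyond the margin passes.

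**Working it through.** **1. The plan's own figure.** Inputs from 11.3: failure 10% in both arms, margin 0.12, one-sided alpha 0.05, power 80%.

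Total N = 2 × (0.09 + 0.09) × (1.645 + 0.842)² / 0.12² = 154.6, so 155. Then 155 / 0.97 = 159.8, so 160. Both figures reproduce. The power table in 11.3 agrees within 2.0 points at full N and within 0.9 point after N is cut by 3%. The sizing therefore treats lost participants as lost information, not as suppressed results.

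**2. Set-up at the margin.** 80 per arm, true failure 10% (continuous) and 22% (SCT). The plan does not name its test, so I assume that non-inferiority is declared when the upper one-sided 95% Wald limit for the difference is below 12 points.

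If a share m of true rebounds in each arm ends as a non-event, the observed failures are 0.10(1 − m) and 0.22(1 − m), and the difference is 12(1 − m) points.

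Error ≈ Φ((0.12 − d)/SE − 1.645), with SE = √[(f_C(1 − f_C) + f_S(1 − f_S))/80].

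Example, m = 0.10: f_C = 0.090, f_S = 0.198, d = 0.108, SE = 0.0549. Then 0.012/0.0549 − 1.645 = −1.426, and the error is 7.7%. Enumerating all binomial outcomes gives 8.3%.

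| Share of rebounds scored as non-events | Difference (points) | Error, normal | Error, enumerated |
|---|---|---|---|
| 0 | 12.00 | 5.0% | 5.4% |
| 5% | 11.40 | 6.2% | 6.7% |
| 10% | 10.80 | 7.7% | 8.3% |

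**3. Later visits catch some.** The outcome counts any of five visits, so a missed rebound that persists can still register. Spread rebounds over weeks 4, 12, 24, 36 and 48 in proportion to interval length (4, 8, 12, 12, 12 of 48) and let each repeat be missed independently.

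| Unrepeated at each visit | Rebounds that persist | Finally missed | Error, enumerated |
|---|---|---|---|
| 5% | none | 5.0% | 6.7% |
| 5% | half | 3.2% | 6.2% |
| 5% | all | 1.3% | 5.7% |
| 10% | none | 10.0% | 8.3% |
| 10% | half | 6.4% | 7.1% |
| 10% | all | 2.8% | 6.1% |

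The documents give neither the unrepeated share nor the persistence; both are assumptions. A simulation of the same question gave 6.3% to 8.4%.

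**4. Leavers, under the binary reading only.** Let loss be uniform over 48 weeks and unrelated to failure. The share of a leaver's rebounds that falls after leaving is (4×4 + 8×12 + 12×24 + 12×36 + 12×48)/48² = 1408/2304 = 0.611.

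| Loss, continuous / SCT | Difference (points) | Error, enumerated |
|---|---|---|
| 3% / 3% | 11.78 | 5.8% |
| 3% / 10% | 10.84 | 8.0% |
| 10% / 3% | 12.21 | 5.0% |

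Only a loss below 3% is documented; the 10% figures are assumptions. With loss concentrated in the continuous arm the observed difference exceeds 12 points, so the bias runs against SCT.

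**The case against.** **Confirmation is deliberate.** Sections 1.5 and 7.2 warn of spurious low-level results, and 2.3 describes blips of 50 to 500 c/ml. A single unrepeated 400 c/ml cannot be assumed to be a failure. This stands and shapes the fix: the adult trial in 2.3 had 9 blips on daily ART against 6 on 5-on/2-off, so counting every single value as an event could itself favour SCT.

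**Missing repeats should be rare.** They are mandatory in both arms, the Trials Units chase overdue data (12.2), and values behind the primary endpoint are checked against source (12.3). This limits the frequency. It does not say how a missing or late repeat is classified, and 7.7 and Appendix 15 can produce late ones in compliant sites.

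**Leavers.** A reader might infer that the plan scores leavers as suppressed. The documents do not say so. Section 11.4 uses a hazard ratio for this outcome, 11.6 gives pilot events an event time, and 11.3 treats losses as lost information. The proportion in 4.2 leaves the binary reading open, but does not impose it.

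**Unequal loss.** A reader might infer heavier loss on SCT from the adult trial, where "all 25 patients in the FOTO arm and 24 of 28 patients (86%) in the daily arm who reached week 24" were suppressed. The text does not support carrying this over. It gives no arm sizes at randomisation, it reports all who stopped as below 50 c/ml at discontinuation, and the one participant listed as lost to follow-up was in the daily arm. Section 9.3 also keeps people who withdraw from the strategy in follow-up where possible.

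**Other outcomes.** RNA below 50 c/ml at weeks 24 and 48 needs no confirmation and offers a partial check, though its handling of missing results is also unstated.

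**Conclusion.** The point holds for raised values without a repeat inside one week: they are non-events under both the binary and the time-to-event methods in 11.6, while other sections allow later repeats. For leavers, the accurate statement is that the text does not specify the handling, and that one of two open readings would count them as suppressed.

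The direction is conditional. With similar rates of missed repeats in both arms and SCT truly worse, the difference moves towards non-inferiority. If 5% to 10% of rebounds were unrepeated, the error at the margin would rise from 5.4% to about 6.2% to 8.3%, taking between half and none of the missed rebounds as persisting to a later visit. It would be 5.7% to 6.1% if all persisted. At 3% loss per arm the leaver effect is 0.4 point (5.4% to 5.8%), which is negligible, and it vanishes or reverses when loss concentrates in the continuous arm. A reader might infer a bias that always favours SCT; these figures do not support that. The issue is modest in size, and worth settling before analysis because the remedy is cheap.

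**What to change.** In 11.6:

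1. **Values without a timely repeat.** Count a scheduled-visit value of at least 50 c/ml as an event at that visit if the next available sample, even one taken after a week, is also at least 50 c/ml, or if no later sample exists. Add a sensitivity analysis that counts every unrepeated value of at least 50 c/ml as an event. Reconcile the confirmation timing in the glossary, 7.7, 11.6 and Appendix 15; which clinical interval is right is for the trial team.
2. **Primary analysis.** Name it as the difference between arms in Kaplan-Meier failure probability at week 48. Censor event-free participants at their last HIV-1 RNA result, and compare the confidence limit with the 12-point margin.
3. **Leavers.** Add a sensitivity analysis that counts participants with no week-48 result as failures. It is not conservative in every case: with 3% missing in each arm it gives 0.97 × 12 = 11.64 points, and with 3% (continuous) and 6% (SCT) it gives 13.98 points.

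The cost is a few lines of wording and two extra runs on data already collected. The downside is that some unrepeated blips may count as failures, in either arm, and the limits widen slightly.
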